### Study endpoints

The primary endpoint is the reduction in performance on cognitive tests defined as follows: After exclusion of local recurrence, decreased detailed neuropsychological assessment score compared to the patient's baseline score before radiotherapy for at least 2 cognitive domains.

Secondary endpoints are:Differences in biomarkers’ concentration between the measurements before RT and: at the end of the RT, RT + 4 weeks, RT + 12 months and RT + 36 months.Changes in MRI images compared to the baseline imaging.Correlations between dosimetry, cognitive decay and MRI abnormalities onset after RT.

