Self-reported Scales	
Mood	Anxiety questionnaire of Goldberg [49]
	Center for Epidemiologic Study Depression Scale [50]
Fatigue	FACIT Fatigue Scale [51]
Memory complaint	MacNair and Khan questionnaire [52, 53]
Quality-of-life	EORTC QLQ-C30 [54]
	EORTC QLQ-BN20 [55]
Care-giver-reported Scales	
Dysexecutive syndrome	ISDC [45, 46]
Autonomy	EIADL [56]

Baseline and trimensual MRI during the medical follow-up are used for extra analysis in order to study white matter abnormalities and cortical atrophy. Moreover, tumor response or progression will be assessed by the Response Assessment in Radio-Oncology working group (RANO) Criteria [25]. The white matter lesion quantification will follow the procedure described by Wahlund et al. [26] using a 4 points scale (0: no lesion; 1: focal lesions; 2: beginning confluence of lesion; 3: diffuse involvement of the entire region). The cortical atrophy quantification will follow the procedure described by Pasquier et al. [27] using a 4 points scale (0: absence of atrophy; 1: mild atrophy; 2: moderate atrophy; 3: severe atrophy). White matter lesion and cortical atrophy is assessed for all key region listed in Table 3. A double blind lecture of the MRI will be done in order to quantify these anomalies. Radiological outcomes will then be correlated with cognitive outcomes.

**Table 3 Tab3:** Regions prospectively explored on MRI and dosimetric analysis

Key regions investigated		
	MRI	Dosimetry
Frontal lobes	*	*
Temporal lobes	*	*
Parietal lobes	*	
Occipital lobes	*	
Cerebellum	*	*
Basal ganglia	*	
Brain Stem	*	*
Hippocampus		*
Corpus Callosum		*
Periventricular white matter		*

* anatomical region investigated

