#### Analysis of evaluation criteria

Based on primary endpoint definition, the estimate of the incidence of cognitive impairment related to radio-induced leukoencephalopathy in our cohort will be made.

An analysis of the dose–response relationship between radiation dose absorbed by different brain structures and cognitive abnormalities observed after radiotherapy will be made using a multivariate Cox model taking into account the delivered dose to the organ of interest and the time occurrence of cognitive complications. An adjustment on risk factors for cognitive complications will be achieved. Similarly for patients with cognitive impairment before radiotherapy, an analysis of potential associated risk factors will be carried out with the use of a multivariate model.

Secondary judgments criteria, including changes in MRI images relative to the reference imaging and changes in series of biological markers between measurements before RT, 4 weeks, 12 month and 36 months after RT, will be analyzed by parametric distribution comparison tests (Z) or nonparametric if needed (Wilcoxon tests).

In addition, an analysis will be conducted of the sensitivity and specificity of the CSCT to demonstrate cognitive impairment by comparing the CSCT performed before radiotherapy and detailed neuropsychological assessment (gold standard) achieved at the same time. More, CSCT decay during follow-up will be analyzed by comparing its results to formal assessment during years after treatment, to study its sensibility in detecting cognitive decrement after radiotherapy.

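### Local recurrence is excluded from the cognitive endpoint but not from the MRI change endpoint, so signal from tumour progression can enter a result read as a radiation effect

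*Protocol article*

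**What the plan says.** Study endpoints gives the primary cognitive endpoint a recurrence rule: "After exclusion of local recurrence, decreased detailed neuropsychological assessment score compared to the patient's baseline score before radiotherapy". The MRI secondary endpoint in the same section reads only "Changes in MRI images compared to the baseline imaging". A further secondary endpoint correlates dosimetry, cognitive decay and the onset of MRI abnormalities, and states no recurrence rule for the MRI part.

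Under Procedures, "White matter lesion and cortical atrophy is assessed for all key region listed in Table 3". The MRI regions in that table are the four lobes, cerebellum, basal ganglia and brain stem. The white-matter scale runs from 0 to 3 by extent, its upper steps being "2: beginning confluence of lesion; 3: diffuse involvement of the entire region". The same paragraph says that "tumor response or progression will be assessed by the Response Assessment in Radio-Oncology working group (RANO) Criteria", and ends with "Radiological outcomes will then be correlated with cognitive outcomes". Procedures also plans to compare dosimetry with the onset of MRI abnormalities, in order to learn about the process of radiation-induced leukoencephalopathy.

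Analysis of evaluation criteria covers "Secondary judgments criteria, including changes in MRI images relative to the reference imaging" with a Z or Wilcoxon test and adds no condition on progression.

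**The concern.** Every patient has a grade III or IV glioma, so later scans can show progression as well as treatment effect. A scale that grades extent does not record cause. Infiltration, growing oedema or recurrent tumour can move a region up the scale in the same way as leukoencephalopathy.

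The authors evidently saw this difficulty for cognition. The endpoint excludes recurrence, and the Discussion notes that disease progression may obscure the cognitive defect. The MRI endpoint faces the same difficulty and has no matching rule. At stake are the MRI change itself and the dose-MRI comparison, on which the study's account of mechanism partly rests. The primary incidence estimate and the sample size are not affected.

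**Working it through.** **1. The two endpoints side by side**

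| Element | Cognitive endpoint | MRI change endpoint |
|---|---|---|
| Reference | Baseline before radiotherapy | Baseline imaging |
| Local recurrence | Excluded | Not mentioned |
| Scoring | Decrease in at least 2 domains | Extent grade 0 to 3 per region, no cause assigned |
| Regions exempted | Not applicable | None (tumour-bearing region and cavity included) |
| Use of RANO result | Not stated, but recurrence is excluded | None stated |
| Interpretation | Impairment related to leukoencephalopathy | No cause named in the endpoint; used against dose to describe leukoencephalopathy |

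**2. What the baseline removes.** Inclusion is after surgery and before radio-chemotherapy. Change from that point cancels tumour or surgical signal that stays stable. It does not cancel signal that appears or grows afterwards, and progression comes afterwards. A region already at grade 3 at baseline cannot worsen.

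**3. Where dose and grade can be paired.** Table 3 marks both MRI and dosimetry for four of the seven MRI regions: frontal lobes, temporal lobes, cerebellum and brain stem. Parietal lobes, occipital lobes and basal ganglia have grades but no regional dose. A region-by-region dose-MRI comparison is therefore possible in four regions only.

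**4. How many scans could be exposed.** The plan states no figure on this point, so there is none to reproduce. Inputs:

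- Scans every 3 months for 36 months (Procedures; 3-year follow-up).
- Median survival M of 15 to 18 months. The Discussion says less than 18; the lower value is assumed.
- Median time to progression m of 6 to 12 months. This is an assumption; the document gives none.
- Exponential times, and every death preceded by progression. Also assumptions.

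With progression rate λ = ln 2 / m and post-progression death rate μ:

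- alive without progression at t: F(t) = exp(−λt)
- alive after progression at t: P(t) = λ/(λ − μ) × [exp(−μt) − exp(−λt)]
- μ is chosen so that F(M) + P(M) = 0.5
- share of scans after progression = ΣP / Σ(F + P) over t = 3, 6, …, 36

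| m | M | λ | μ | ΣP | ΣF | All scans after progression | At month 12 |
|---|---|---|---|---|---|---|---|
| 12 | 15 | 0.0578 | 0.3598 | 0.786 | 4.625 | 0.786/5.411 = 14.5% | 0.093/0.593 = 15.7% |
| 12 | 18 | 0.0578 | 0.1824 | 1.508 | 4.625 | 24.6% | 26.4% |
| 6 | 15 | 0.1155 | 0.1084 | 2.805 | 2.376 | 54.1% | 59.1% |
| 6 | 18 | 0.1155 | 0.0770 | 3.691 | 2.376 | 3.691/6.068 = 60.8% | 0.441/0.691 = 63.8% |

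The range is about 15% to 61% of all scans in living patients, and 16% to 64% at month 12. These are shares of scans taken after progression. They are not shares with a raised grade.

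**5. What a raised grade would do to a crude rate (illustration).** Let r be the share of patients with a true radiation change and q the share whose grade rises because of progression, taken as independent. The observed share is 1 − (1 − r)(1 − q). With r = 0.30 this gives 0.37 at q = 0.10, 0.475 at q = 0.25 and 0.65 at q = 0.50. Both r and q are free inputs, so this shows only how the rate would respond.

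**The case against.** An article condenses the full protocol. The grading follows two published procedures that are not reproduced here, and an imaging manual or analysis plan may say how readers treat cavity, oedema and tumour. That is fair for reader instructions. It does not dispose of the point, because the article does settle recurrence for one endpoint and leaves it out of the one listed beside it. Which scans count is part of the endpoint.

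The endpoint names no cause, so saying that tumour signal is counted as radiation damage goes beyond its wording. That stands. The radiation reading comes from the stated use of MRI abnormalities against dose.

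The MRI-cognition correlation may already inherit the exclusion, since the defined cognitive outcome applies after recurrence is removed. That also stands. It is not established that the two outcomes rest on different patients when correlated. The gap is clear for MRI change on its own and for the dose-MRI comparison.

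A reader might infer that the dose-MRI correlation is biased upward, because the tumour region receives the highest dose. The document gives no dose map, and only four MRI regions have a regional dose, so neither direction nor size can be fixed.

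A reader might also want to drop the tumour-bearing lobe, or score only the opposite hemisphere. The Background lists radio-necrosis and edema among possible radiation mechanisms. Removing that lobe could discard true effect and, if it is the high-dose region, the top of the dose range. Table 3 records no side, so a contralateral score cannot be presumed to exist.

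**Conclusion.** The point holds as an inconsistency between endpoints. Recurrence is excluded for cognition and not for MRI change, and no stated rule uses the planned RANO assessment to separate the two sources of signal. Following the text as written would let progression contribute to a result used to describe radiation-induced leukoencephalopathy.

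How much it contributes is unknown. The 15% to 61% describes exposure only. It depends mainly on the assumed 6 to 12 month median progression, and also on exponential times and on deaths following progression. It is not an estimate of bias. The matter concerns secondary endpoints, and the correction is cheap enough to be worth making.

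**What to change.** In Study endpoints and in Analysis of evaluation criteria, state that the main analysis of MRI change, and of the dose-MRI and MRI-cognition correlations, uses scans before RANO progression, matching the recurrence rule of the cognitive endpoint. Report the same analyses on all scans as a sensitivity analysis.

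Results with and without the tumour-bearing region may be shown as a further sensitivity analysis. Keep that region in the main score.

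No new imaging is needed for the progression rule, since RANO assessment is already planned. The cost is fewer late scans in the main analysis, and so less information on late MRI change; the all-scan analysis keeps those scans in view.

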### Procedures

Figure 1 gives an overview of the study flowchart. Patients’ inclusion occurs after surgery and before radio/chemotherapy (Baseline). At this time, individual information including demographic information, medical background and tumor characteristic are collected.

**Fig. 1 Fig1:**
[figure not shown]
Study procedure

Every 3 months, once the MRI of the patient is done, a medical visit occurs during which a short cognitive assessment is performed (the CSCT).

Cognitive tests, scales and questionnaires used for the formal assessment are listed in Table 2. An extensive evaluation lasting 2 h is performed with a trained neuropsychologist, followed by self-reported and caregiver-reported scales and questionnaires. The explored domains are intellectual efficiency, general functioning, verbal and visual episodic memory, attention, executive functioning, language, visuospatial and visuoconstructive abilities, mood, fatigue, quality-of-live, subjective complaints and autonomy. The formal assessment occurs at baseline and yearly after radiotherapy. In case of CSCT score decrement during follow-up the next yearly formal assessment is performed earlier. CSCT decrement is defined as a loss of 1 standard deviation compared to baseline (given its low learning-effect and good stability in controls [22]), during two consecutive assessments. The necessity of detecting a decrement during two visits permits to insure that a variation in score is not due to a transitory cause like an infection or fatigue, which is reversible and not linked to leukoencephalopathy. This procedure will allow to study the nature, course and incidence of cognitive decrement following radiotherapy in this population. At baseline and during the follow-up, the CSCT will be compared to the formal cognitive assessment to study its sensibility to detect impairments in this context.

**Table 2 Tab2:** Tests and questionnaires used for the cognitive, mood and behavioral assessment

Domain	Tests, scales and questionnaires
Cognitive assessment	
Intellectual efficiency	National Adult Reading Test (French version) [38]
General functioning	Mini Mental State Examination [39]
	Montreal Cognitive Assessment [40]
	Dementia Rating Scale-2 [41]
Verbal episodic memory	RLRI-16 (Adaptation of the Grober-Buschke test) [42]
Visual episodic memory	Rey-Osterrieth Complex Figure [43]
Executive functions and Attention	Digit Span forward [44]
	Digit Span backward [44]
	Letter-number sequencing [44]
	Categorical and phonetic word fluency [45, 46]
	Trail Making Test [45, 46]
	Computerized Speed Cognitive Test [22]
	Stroop color-word Test [45, 46]
Langage	Boston Naming Test [47]
	Token Test [48]
Visuospatial and visuoconstructive functions	Rey-Osterrieth Complex Figure [43]
Self-reported Scales	
Mood	Anxiety questionnaire of Goldberg [49]
	Center for Epidemiologic Study Depression Scale [50]
Fatigue	FACIT Fatigue Scale [51]
Memory complaint	MacNair and Khan questionnaire [52, 53]
Quality-of-life	EORTC QLQ-C30 [54]
	EORTC QLQ-BN20 [55]
Care-giver-reported Scales	
Dysexecutive syndrome	ISDC [45, 46]
Autonomy	EIADL [56]

Baseline and trimensual MRI during the medical follow-up are used for extra analysis in order to study white matter abnormalities and cortical atrophy. Moreover, tumor response or progression will be assessed by the Response Assessment in Radio-Oncology working group (RANO) Criteria [25]. The white matter lesion quantification will follow the procedure described by Wahlund et al. [26] using a 4 points scale (0: no lesion; 1: focal lesions; 2: beginning confluence of lesion; 3: diffuse involvement of the entire region). The cortical atrophy quantification will follow the procedure described by Pasquier et al. [27] using a 4 points scale (0: absence of atrophy; 1: mild atrophy; 2: moderate atrophy; 3: severe atrophy). White matter lesion and cortical atrophy is assessed for all key region listed in Table 3. A double blind lecture of the MRI will be done in order to quantify these anomalies. Radiological outcomes will then be correlated with cognitive outcomes.

**Table 3 Tab3:** Regions prospectively explored on MRI and dosimetric analysis

Key regions investigated		
	MRI	Dosimetry
Frontal lobes	*	*
Temporal lobes	*	*
Parietal lobes	*	
Occipital lobes	*	
Cerebellum	*	*
Basal ganglia	*	
Brain Stem	*	*
Hippocampus		*
Corpus Callosum		*
Periventricular white matter		*

* anatomical region investigated

The need for a biological marker of cognitive disorders has proven to be urgent, both for diagnosis and for monitoring of the diseases. Among the advantages that such markers may bring, we emphasize the possibility of early and even preclinical diagnosis of the disease with the subsequent correct treatment of disease by the medical team. Biomarkers for cognitive impairment have been an issue in recent years. The value of a variety of these markers, like amyloid beta or tau, has been evaluated and discussed [28]. Besides proteins, microRNAs have also demonstrated their potential as non-invasive biomarkers from blood and serum for a wide variety of human pathologies [29]. A deregulation of microRNA expression might be involved in neurological dysfunction or neurodegenerative processes. A recent serum profiling of Alzheimer disease patients provided evidence that expression changes of circulating miRNAs may be valuable biomarkers for this neurological disease [20]. In addition, microparticles have been implicated to have pathological roles in many diseases such as Alzheimer’s disease. The consensus among recent studies is that increased levels of specific types of microparticles in plasma may represent reliable biological markers for the onset and progression of central nervous system diseases [30].

Consequently, plasmatic classical biomarkers as S-100B protein, isoprostane 8,12-*iso*-iPF_2α_-VI, homocysteine and new ones, as micro RNA and microparticules (see Table 4) will be sampled in blood at baseline, 4 weeks, 12 months and 36 months after the end of radiotherapy. These biomarkers could be potential blood predictors of cognitive impairments [17, 19–21] and thus their concentration evolution after radiations will be analyzed. Additional blood sample tubes are stored to constitute a biological collection for future investigations about others biomarkers.

**Table 4 Tab4:** Biomarkers sampled in blood

Classical biomarkers correlated with cognitive impairments	S-100B protein [GenBank : NP_006263]
	8,12-iso-iPF2a-VI isoprostane
	Homocysteine [GenBank : NP_060084]
	microRNAs
New biomarkers	brain-miR-112 [GenBank : AF480510]
	brain-miR-161 [GenBank : AJ535829]
	hsa-let-7d-3p [GenBank : LM380164]
	hsa-miR-5010-3p [GenBank : LM38284]
	hsa-miR-26a-5p [GenBank : LM378769]
	hsamiR-1285-5p [GenBank : LM383022]
	hsa-miR-151a-3p [GenBank : LM379262]
	hsamiR-103a-3p [GenBank : LM378788]
	hsa-miR-107 [GenBank : LM378791]
	hsa-miR-532-5p [GenBank : LM379811]
	hsa-miR-26b-5p [GenBank : LM378770]
	hsa-let-7f-5p [GenBank : LM378754]
	microparticles

Finally, histograms of dose-volumes (HDV) of specific organs and areas are collected to study the relation between the radiation doses received by these structures and the cognitive decrements observed. Indeed, some authors showed correlations between specific structures and cognitive performances [31, 32] but few data are available and thus these relations need to be explored. More, dosimetry is compared with onset of abnormalities on MRI to improve knowledge about radio-induced leukoencephalopathy process. Structures prospectively investigated are listed in Table 3.

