### Objectives

The purpose of the EpiBrainRad study is to establish a cohort of patients treated with radiotherapy for a high grade glioma.

The main objective is to estimate the cognitive impairment incidence related to radio-induced leukoencephalopathy in this population.

Secondary objectives are:To study the impact of associated risk factors on leukoencephalopathy development, including individual factors and treatment.Biologic markers of neurologic degradation will be studied to evaluate the correlations between cognitive impairments and biological abnormalities.Specific organs dosimetry (such as hippocampus, temporal lobes, corpus callosum, peri-ventricular white matter, posterior fossa) correlated with radiologic abnormalities on magnetic resonance imagery (MRI) and clinical symptoms will be analyzed to better understand the evolution of radio-induced leukoencephalopathy.Finally, the assessment of the sensibility and specificity of a quick cognitive test, *the Computerised Speed Cognitive Test* [22], to detect a cognitive decrement during the follow up of the patients.

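### The CSCT is one of the tests in the formal assessment used as its gold standard, so as written its apparent sensitivity and specificity are biased upward, by a modest amount

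*Protocol article*

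**What the plan says.** - **Content of the formal assessment** (Procedures): "Cognitive tests, scales and questionnaires used for the formal assessment are listed in Table 2". In Table 2, the executive functions and attention group includes "Computerized Speed Cognitive Test [22"]. The six other entries in that group are digit span forward, digit span backward, letter-number sequencing, word fluency, Trail Making and the colour-word test.
- **Accuracy analysis at baseline** (Analysis of evaluation criteria): sensitivity and specificity come from "comparing the CSCT performed before radiotherapy and detailed neuropsychological assessment (gold standard) achieved at the same time".
- **Accuracy analysis in follow-up** (same section): "CSCT decay during follow-up will be analyzed by comparing its results to formal assessment during years after treatment". Procedures announces the same comparison for both periods: "the CSCT will be compared to the formal cognitive assessment to study its sensibility to detect impairments in this context".
- **Objective served** (Objectives, last secondary objective): "the assessment of the sensibility and specificity of a quick cognitive test".
- **Case rule on the formal assessment** (Study endpoints): "decreased detailed neuropsychological assessment score compared to the patient's baseline score before radiotherapy for at least 2 cognitive domains". No rule is given for combining tests within a domain.
- **CSCT positivity in follow-up** (Procedures): "CSCT decrement is defined as a loss of 1 standard deviation compared to baseline", required at two consecutive visits.

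Nowhere does the article say that the CSCT is left out when the formal assessment serves as the reference.

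**The concern.** An accuracy study needs a reference that does not contain the test being judged. Otherwise part of the agreement is the test agreeing with itself. A low CSCT score then makes the patient both test-positive and more likely to be reference-positive. A normal score does the reverse. Both sensitivity and specificity are pushed up.

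The Background proposes the CSCT as an alarm that starts a full assessment, and the Discussion says that the study will help validate it in this population. Its accuracy figures would therefore be used to decide how far a short test can stand in for a long one. A reader of the results could not remove the overlap without test-level data.

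**Working it through.** **The plan's own figures.** The article states no accuracy figure and no sample size for the CSCT analysis. Its only computed figure is the sample size for the incidence estimate. With z = 1.95996 and an assumed half-width of 0.05, z² × 0.2 × 0.8 / 0.05² = 245.9 and z² × 0.5 × 0.5 / 0.05² = 384.1, which match the stated 246 and 384. That figure has no bearing on this point.

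**Direction.** Suppose a domain counts as impaired when one test (or two tests) falls below a cut at or beyond the CSCT's own positivity cut. Adding the CSCT can then only add reference cases, and every added case is CSCT-positive. Those patients move from false positive to true positive:

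- sensitivity = TP / (TP + FN): TP rises and FN is unchanged, so it rises;
- specificity = TN / (TN + FP): FP falls and TN is unchanged, so it rises.

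If the domain is scored by a mean, patients can move both ways, so the direction was checked by simulation.

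**Size: assumed inputs.** None of these is in the article except the test counts, taken from Table 2.

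- 400,000 simulated patients, 35% of them shifted by −1 SD.
- Six domains with 3/1/1/6/2/1 tests apart from the CSCT: general functioning, verbal memory, visual memory, executive/attention, language, visuospatial.
- Correlation from a general factor 0.2 or 0.4, plus 0.2 within domain.
- CSCT positive below −1 SD, on a single occasion.
- Reference positive if at least two domains are impaired.

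| Domain impaired if | General-factor correlation | Sensitivity, CSCT in / out | Gap (points) | Specificity, CSCT in / out | Gap (points) |
|---|---|---|---|---|---|
| any test < −1.5 SD | 0.2 | 0.506 / 0.496 | 1.0 | 0.868 / 0.857 | 1.1 |
| any test < −1.5 SD | 0.4 | 0.591 / 0.585 | 0.6 | 0.888 / 0.881 | 0.7 |
| any test < −1 SD | 0.2 | 0.397 / 0.389 | 0.8 | 0.931 / 0.910 | 2.1 |
| any test < −1 SD | 0.4 | 0.456 / 0.450 | 0.6 | 0.950 / 0.936 | 1.4 |
| mean < −1 SD | 0.2 | 0.495 / 0.485 | 1.0 | 0.867 / 0.861 | 0.6 |
| mean < −1 SD | 0.4 | 0.552 / 0.545 | 0.7 | 0.899 / 0.894 | 0.5 |
| two tests < −1 SD | 0.2 | 0.484 / 0.470 | 1.4 | 0.891 / 0.872 | 1.9 |
| two tests < −1 SD | 0.4 | 0.542 / 0.533 | 0.9 | 0.917 / 0.905 | 1.2 |
| two tests < −1.5 SD | 0.2 | 0.608 / 0.593 | 1.5 | 0.824 / 0.815 | 0.9 |
| two tests < −1.5 SD | 0.4 | 0.687 / 0.679 | 0.8 | 0.846 / 0.839 | 0.7 |

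In a domain with a single test, the two-test rule means that one test.

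**Check of the first row by hand.** The reference is positive in 0.385 of patients without the CSCT and 0.393 with it, so 0.008 move. TP without is 0.385 × 0.496 = 0.191; with, (0.191 + 0.008) / 0.393 = 0.506. TN is 0.615 × 0.857 = 0.527; with the CSCT, 0.527 / 0.607 = 0.868. Both agree with the table.

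**A CSCT that is pure noise** (any test < −1.5 SD, correlation 0.2, two domains): sensitivity 0.178 in against 0.159 out, specificity 0.854 against 0.842. Sensitivity plus specificity is 1.032 in and 1.001 out. A useless test should give 1.

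**If one impaired domain is enough** (same any-test rule): specificity rises by about 3 points for an informative CSCT and about 6 for a noise CSCT. This matters at baseline. The two-domain rule in Study endpoints is a decrease from the patient's own baseline, so it cannot define impairment at baseline, and the article gives no other rule for it.

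**The case against.** **The CSCT may not enter the reference score.** The caption of Table 2 is broader than the formal battery, and elsewhere the article speaks of the CSCT and the detailed assessment as two things. Which tests enter a domain score is also a detail that a condensed article may leave to a fuller document, not shown here. This stands as a caution: that document may already exclude the CSCT. It does not remove the point. The article says outright that Table 2 gives the content of the formal assessment, the CSCT is in Table 2, and the same assessment is named as gold standard. Followed as written, the reference contains the index test.

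**The effect is inside sampling error.** Suppose all 400 patients were assessable and the article's 0.2 to 0.5 were the case fraction, giving 80 to 200 cases. The 95% half-width for a sensitivity of 0.5 would be 1.96 × √(0.25/80) = 0.110 to 1.96 × √(0.25/200) = 0.069. For a specificity of 0.87 in 200 to 320 non-cases it would be 0.047 to 0.037. Early deaths would widen these. This is correct and keeps the point modest. But sampling error has no direction, while this error always favours the test and does not shrink with more patients.

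**In follow-up the overlap is looser.** Positivity there needs two consecutive low scores, so the CSCT score inside one formal assessment is not the whole index result. This stands. The simulation is single-occasion and describes the baseline analysis better than the follow-up one.

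**Stronger readings that the article does not support.** A reader might infer that a CSCT fall alone supplies one of the two impaired domains. That holds only if any single test makes a domain impaired, a rule that the article does not state. A reader might also infer that the CSCT should leave the primary endpoint. Incorporation affects only the accuracy analysis. The Background names processing speed among the functions most affected by radiation and says that the CSCT was developed to measure it, so removing it could make the primary endpoint less sensitive. That a CSCT fall brings the next formal assessment forward affects its timing and does not disqualify the test as an outcome component.

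**Conclusion.** The point holds for the CSCT accuracy objective. The article puts the CSCT inside the assessment that serves as its gold standard at baseline and its comparator in follow-up, and this biases apparent sensitivity and specificity upward. Under the assumed two-domain scoring rules, both measures rose in all ten scenarios, by about 0.5 to 2 points. The figure rests on assumed correlations, cuts and combination rules, because the article gives none. It would be larger if the CSCT weighed more in its domain or if one impaired domain were enough. The size in follow-up, under the two-visit rule, was not calculated. The documents do not support a claim of large inflation, and the primary incidence estimate is not affected by this point.

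**What to change.** Add one sentence to the analysis section: for all CSCT accuracy analyses, at baseline and in follow-up, the formal assessment is scored without the CSCT, and the executive and attention domain is scored from its six other tests. If the full protocol or the analysis plan already does this, the article's description of the gold standard should be aligned with it.

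No new data, visits or patients are needed, and the domain keeps six tests. The cost is that the reference for these analyses differs by one test from the score behind the primary endpoint, which the sentence should say. The primary endpoint stays as it is.
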